### Additional substudies

#### Change mechanisms of EMDR and ImRs

This study aims to test the proposed (differential) mediators of EMDR and ImRs (i.e., valence and vividness of the traumatic memory, and the strength of the encapsulated belief). We hypothesize that (1) the effect of change in the encapsulated belief on PTSD symptom change is stronger for ImRs and (2) the effect of change in memory vividness on PTSD symptom change is stronger for EMDR. As memory valence changes have been observed in both treatments and thus findings are mixed [124–126], we will not make specific predictions for this mediator. In order to test the causality of effects, which is currently unknown, we will also test the reverse relationships. As an exploratory analysis, we might also conduct a model selection procedure, but the main focus lies on testing the predictors in separate models.

#### Predictors of treatment outcome and PTSD severity: personality disorder psychopathology and trauma characteristics

The aim of this study is to examine whether comorbid personality disorder psychopathology and trauma characteristics are related to (differential) treatment outcome. In clinical practice, patients with comorbid personality disorder psychopathology are often assumed to benefit less from treatment focused on their syndrome disorder compared to patients without comorbid personality disorder psychopathology [127, 128]. However, there is mixed evidence regarding the effect of comorbid personality disorder psychopathology on treatment outcome in PTSD patients [129]. In addition, mixed results were also found for the effect of trauma characteristics, including type and severity of childhood trauma [129].

Trauma characteristics may also play a role in the prediction of PTSD symptoms, which in turn might predict differential treatment response. Whilst sexual and physical abuse in childhood can give rise to PTSD [130], several studies have suggested that other types of childhood maltreatment (e.g., emotional abuse or neglect) can also result in PTSD although not officially qualifying as traumatic experiences according to the DSM-5 [131–133]. Therefore, one aim will be to explore the unique relationships between childhood abuse and neglect and PTSD severity. A model fit procedure will also be conducted to test which of these types remain in a final model.

#### Role of emotions

This study will investigate patterns of change over time of emotions (i.e., fear, shame, guilt, sadness, disgust, and anger) and PTSD symptoms between sessions and assessments. Temporal relations between emotions and PTSD symptoms will be examined. More specifically, we will examine (1) whether changes in emotions precede changes in PTSD symptoms, (2) whether changes in PTSD symptoms predict changes in emotions, and (3) whether there is a reciprocal relationship between changes in emotions and PTSD symptoms.

#### Role of cognitions

Changes in trauma-related cognitions have been found to precede subsequent changes in PTSD symptoms during CPT [134]. In this study, we will examine if changes in trauma-related cognitions (measured with the PTCI) will also precede and predict changes in PTSD symptoms in EMDR and ImRs and, therefore, are an important underlying mechanism of change in PTSD treatment in general beyond CPT.

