## Background

Posttraumatic stress disorder (PTSD) can develop after exposure to a traumatic event. PTSD is a chronic and severe mental disorder characterized by four main clusters of symptoms, including re-experiencing the traumatic event, avoidance of trauma-related stimuli, negative feelings or thoughts, and increased arousal [1]. Based on meta-analytic reviews and practice guidelines, trauma-focused cognitive behavior therapy (TF-CBT) and eye movement desensitization and reprocessing (EMDR) are recommended as first-line treatments for PTSD [2, 3]. However, the efficacy of traditional (stand-alone) PTSD treatments for patients with childhood trauma-related PTSD (Ch-PTSD) is more uncertain [4–7]. Individuals with Ch-PTSD are characterized by more complex symptoms, such as interpersonal difficulties, emotional regulation problems, impaired self-concept, and memory and attention difficulties [5, 7–9]. A meta-analysis on psychological treatments for Ch-PTSD found evidence that patients with Ch-PTSD can be treated effectively with trauma-focused treatments [7]. However, research into the effectiveness of treatments for patients with Ch-PTSD is limited as existing studies on the effectiveness of PTSD treatments mainly focus on survivors of adult-onset trauma, resulting in an underrepresentation of survivors of childhood-onset trauma [7, 10].

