#### Primary outcome

##### PTSD severity

The primary outcome is the change in the severity of the DSM-5 PTSD symptoms between the baseline and follow-up 1 assessments, assessed with the Clinician Administered PTSD Scale for DSM-5 (CAPS-5 [54]). The CAPS-5 is a structured interview consisting of 30 5-point Likert scale items ranging from 0 (absent) to 4 (extreme/incapacitating) rating the 20 DSM-5 PTSD symptoms in the past month. In the current study, the CAPS-5 assesses responses to all traumatic events that have been identified with the LEC-5. The CAPS-5 has demonstrated good reliability and validity [55–57].

The assessment period of the CAPS-5 (i.e., past month) at the T3 assessment overlaps with the treatment period in the once-weekly frequency condition. Therefore, we chose to focus on change between baseline and follow-up 1 instead of baseline and T3 since the follow-up 1 assessment takes place several weeks after treatment has finished and does not overlap with the treatment period (i.e., administered 8–12 weeks after treatment has finished in the once-weekly frequency condition and 16–18 weeks after treatment has finished in the twice-weekly treatment condition).

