#### Secondary outcomes

##### Self-reported PTSD symptoms and trauma-related feelings

Self-reported PTSD symptoms are measured using the PTSD Checklist for DSM-5 (PCL-5 [58]). The PCL-5 consists of 20 5-point Likert scale items ranging from 0 (not at all) to 4 (extremely). We created two versions of the PCL-5; one version assessing self-reported PTSD symptoms with respect to the index trauma and the other one for all traumatic experiences except of the index trauma. The time frame was changed from the past month to the past week. Psychometric properties of the PCL-5 were found to be good [59–61].

Seven single-item scales were added to the PCL-5 [38, 62], see Additional file 1: Appendix D. Six items were included to assess trauma-related feelings (i.e., feelings of shame, anger, guilt, disgust, sadness, and anxiety) with respect to the index trauma and for all traumatic experiences except of the index trauma. An additional item was included to assess feelings of happiness in the past 7 days, for secondary analysis purposes. The additional items will not be used for computation of the total PCL-5 score.

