##### PTSD-related cognitions

The Posttraumatic Cognitions Inventory (PTCI [63]) is a 33-item questionnaire measuring trauma-related cognitions across three domains (i.e., negative cognitions about self, negative cognitions about the world, and self-blame). The items are rated on a 7-point Likert scale ranging from 1 (totally disagree) to 7 (totally agree). The PTCI has demonstrated satisfactory psychometric properties [63].

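### The cognition substudy, and less strongly the emotion substudy, tests precedence of a PTSD outcome that by the protocol's own definition includes negative feelings or thoughts, so predictor and outcome share construct content

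*Protocol article*

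**What the plan says.** The Background describes PTSD by four clusters: "re-experiencing the traumatic event, avoidance of trauma-related stimuli, negative feelings or thoughts, and increased arousal". Under PTSD severity, the CAPS-5 is described as "rating the 20 DSM-5 PTSD symptoms in the past month". The PCL-5, the DSM-5 self-report checklist, has 20 items. The article describes no version of either score that leaves a cluster out.

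Role of cognitions asks whether "changes in trauma-related cognitions (measured with the PTCI) will also precede and predict changes in PTSD symptoms in EMDR and ImRs". If so, cognitions would count as a mechanism of change in PTSD treatment generally, beyond the therapy in which this was found before. The PTCI covers "negative cognitions about self, negative cognitions about the world, and self-blame".

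Role of emotions asks "whether changes in emotions precede changes in PTSD symptoms" for fear, shame, guilt, sadness, disgust and anger. It also tests the reverse direction and a reciprocal relation, and states no mechanism conclusion.

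Statistical analyses assigns both questions to mediation models, with mixed regression of the Granger type as the example. One related safeguard exists for the feeling items that were added to the PCL-5: "The additional items will not be used for computation of the total PCL-5 score".

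**The concern.** A Granger-type test asks whether the predictor at one time point improves prediction of the outcome at the next, given the outcome's own past. If the outcome is a total that contains negative feelings or thoughts, a measure of negative thoughts can pass this test by predicting that part of the total. It need have no influence on re-experiencing, avoidance or arousal.

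Secondary objective 6 is a question about mechanism. On a full total, a positive result cannot separate two readings: cognitions drive the rest of the disorder, or negative cognitions forecast negative cognitions. The safeguard for the added feeling items stops an item from being counted on both sides, but the cluster that belongs to the 20 standard symptoms stays in the total.

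**Working it through.** The article gives no figure for these substudies, so there is none to reproduce. The check is one of content, followed by an illustration of size.

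**Content.** The Background puts negative feelings or thoughts inside PTSD. The CAPS-5 rates all 20 symptoms. The PCL-5 is the 20-item checklist for the same diagnosis. The PTCI measures negative thoughts about self and world, and self-blame. The construct therefore lies on both sides of the cognition model. Neither substudy section removes or separates the cluster.

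**Why lagging does not remove it.** Let C be feelings/thoughts and S the other symptoms, independent of each other, with autocorrelations φC and φS. The total is Y = aS + bC + error and the predictor is X = C. Regressing Y(t) on Y(t−1) and X(t−1), the coefficient of X is

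b × (φC − λφS),

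where λ is the reliability of Y with C held fixed. It is zero only if φC = λφS, for example with equal stability and no error. With 5 of 20 symptoms shared, b = 5/20 = 0.25:
- φC = 0.7, φS = 0.5, λ = 1: 0.25 × (0.7 − 0.5) = 0.05.
- φC = φS = 0.7, λ = 0.9: 0.25 × (0.7 − 0.9 × 0.7) = 0.0175.

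The true effect of C on S is zero in both cases.

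**Number of time points.** The standard assessments are T1, T2, T3, follow-up 1 and follow-up 2, which makes 5. The Procedure section and the notes to Table 1 name the PCL-5 with its added items, and the mediator items, as completed before each session from session 2. With at most 12 sessions that gives 12 − 1 = 11 points. The PTCI is not described as a session measure, so 5 is the relevant number for cognitions.

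**Simulation A (200 patients, 5 assessments, no true cross-effect, clustered standard errors).** Assumed: number of shared symptoms, stability, and latent correlation of the predictor with the shared content. Item noise largely averages out over 20 items. Rate of a significant result for X preceding Y:

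| Setting | 2 shared | 3 | 5 | 7 |
|---|---|---|---|---|
| φC 0.7, φS 0.5, identical construct | about 12% | 22% | 52% | 82% |
| φC 0.7, φS 0.5, latent correlation 0.5 | 6% | 10% | 15% | 28% |

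With equal stability the rate is 5 to 8% across 2 to 7 shared symptoms. With the shared symptoms removed from the outcome it is about 4 to 8%.

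**Simulation B (200 patients, 400 runs, shared weight 0.25, identical construct).** This one varies measurement error:

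| φC / φS, reliability | 5 points, total | 5 points, cluster removed | 11 points, total |
|---|---|---|---|
| 0.7 / 0.7, 1.0 | 5.0% | 4.0% | 5.8% |
| 0.7 / 0.7, 0.9 | 12.2% | 5.5% | 20.3% |
| 0.7 / 0.7, 0.8 | 27.0% | 5.2% | 54.0% |
| 0.8 / 0.6, 0.9 | 69.3% | 4.5% | 97.8% |

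The 11-point column applies to the emotion items only. Over all settings run, the cluster-removed rate lay between 3.3% and 7.5%. The simulation standard error near 5% is √(0.05 × 0.95 / 400) = 0.011, about 1.1 percentage points.

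**The case against.** The strongest objection is that both sections speak only of PTSD symptoms. They name no instrument or score, and an article may leave the choice of score to the full plan. That is fair as to scoring detail. But the article does fix the predictor, the outcome as defined in its Background, the model family, and for cognitions the inference. That inference does not follow from a full score, whichever of the two instruments supplies it.

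Four further points stand and limit the finding:
- The overlap is of construct. A reader might infer that the same items sit on both sides. The documents do not support that: the PTCI is a separate instrument, and the added feeling items are kept out of the PCL-5 total.
- A reader might infer that a false positive is close to certain. The rates above 50% need the predictor to be the same construct as the shared content, together with a stability gap, appreciable measurement error or many time points. The PTCI has three domains of its own, and a single emotion is unlikely to equal a whole cluster. The 11-point rates cannot be applied to the PTCI at all.
- A reader might extend the mechanism conclusion to emotions. It is stated for cognitions only, and the emotion section tests both directions. The reverse tests do not separate the constructs, however, since the total contains the cluster in that role too.
- The article lists no individual items, so it cannot be checked whether fear, anger or disgust also overlap with symptoms in the clusters that would be kept. For this reason, and for comparability with earlier work on totals, replacing the total as main outcome is debatable. Reporting both scores is not.

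**Conclusion.** The point holds as one about interpretation of two secondary substudies, mainly Role of cognitions. Predictor and outcome share content by the protocol's own definition, and adjusting for the previous total protects only under special conditions.

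The direction of the problem and the effect of removing the cluster are the same in both simulations. The size is not known, because the number of shared symptoms, the stabilities, the reliabilities and the correlation between the PTCI and the cluster are all assumptions. For 5 assessments in simulation A, the plausible span is from about 5% (equal stability, little error), through 6 to 28% (unequal stability, latent correlation 0.5), to 12 to 82% (unequal stability, identical construct), against about 5% with the cluster removed. Simulation B adds that measurement error alone can lift the rate to 12 to 27% at a quarter share.

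The frequency comparison on the CAPS-5 uses randomised groups and no such predictor, so it is not affected.

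**What to change.** In Role of cognitions and Role of emotions, or in the analysis plans of these substudies, pre-state a parallel lagged analysis. Its outcome is the PTSD score without the negative feelings/thoughts cluster, that is, the re-experiencing, avoidance and arousal items of the PCL-5 or CAPS-5. Report it next to the full total, and name the instrument used. State that cognitions will be called a mechanism of change only if the result also holds on the reduced score. Settle this before the data are analysed, so that the choice of score is not made with results in view.

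The cost is a sentence or two of text and one more analysis per substudy. All items are already collected. The reduced score is shorter and slightly less reliable, and it is less comparable with earlier studies, which is why the full total stays alongside it.

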#### Memory of previous session

A possible working mechanism of the effect of session frequency on treatment outcome is the amount of episodic memory details of the previous session. Rich episodic memory details and vivid re-experiencing of these details have been shown to quickly decay within the scope of days [135, 136]. Repeatedly activating a memory conserves its unique properties and long-term maintenance [137]. Therefore, this study aims to investigate if the effect of session frequency on treatment outcome is mediated by the amount of details patients and therapists remembered and retrieved from the previous session.

#### Learned helplessness

Learned helplessness refers to a pattern of thoughts and behavior instigated by repeated or intense, uncontrollable adverse events, that increases the likelihood of psychopathology, especially depression [138]. This study aims to build on earlier analyses investigating the impact of trauma-focused treatments on levels of learned helplessness [139]. Further, the role of learned helplessness as a possible mediator of change, especially for participants who have a comorbid depression diagnosis, will be investigated.

#### Prediction of (differential) treatment response

Patients with PTSD vary substantially in their response to trauma-focused treatments [140]. More insight into factors associated with treatment outcome in PTSD is therefore needed. The aim of this study is to optimize treatment selection by examining patient characteristics that predict (differential) treatment response across treatment types (EMDR and ImRs) and treatment frequencies (twice-weekly and once-weekly).

#### Perspectives of patients and therapists

Qualitative studies will focus on the perspectives of patients and therapists on the treatments. These studies will focus on, among others, the experiences with the frequency of the sessions and the mechanisms of change in ImRs. In-depth interviews will be performed with a subsample of the study population, including patients and therapists.

#### Network models of PTSD symptoms

The network approach is an alternative approach to conceptualize mental disorders [141]. Network analysis will, therefore, be performed to gain more insight into the network structure of (complex) PTSD symptoms. More specifically, this study aims to investigate the cross-sectional structure of (complex) PTSD symptoms (e.g., connectivity, centrality) of patients before the start of the treatment [142], as well as its change during the course of treatment [143].

#### Sudden gains and treatment outcome

A sudden gain is defined as a large improvement in an outcome variable experienced by a patient between two consecutive sessions. Research on sudden gains in treatments for PTSD suggests that they are positively associated with treatment outcome [144]. However, there is a lack of knowledge about what contributes to sudden gains in treatment of PTSD as well as the role that treatment frequency may play. We hypothesize that (1) therapeutic alliance, memory and learning, and reluctance and avoidance predict sudden gains, (2) the occurrence of sudden gains in the twice-weekly sessions is higher than in the once-weekly sessions, and (3) sudden gains predict treatment outcome.

### Oversight and monitoring

#### Data monitoring and management

The study is guided by the study board, which acts as the steering committee. The study board is composed of the principal investigator, co-principal investigator, junior investigators, and site investigators (see Additional file 1: Appendix J for the names, roles, and responsibilities of the study board members). The study board meets every month and reviews the progress of the study. In addition, final decisions on changes to the protocol, publications, and reporting will be made by the study board. Decisions will be made in consensus or, if necessary, by a majority vote of the study board. Moreover, publication agreements are being made in the study board meetings.

The study will not be audited by independent auditors because of limited study resources. However, to preserve the integrity of the trial, trial processes and documents will be reviewed by the study board members. In addition, there is no data monitory committee as the study involves minimal risk. Both interventions are part of regular care and effective and safe for patients with Ch-PTSD [11]. The data will be monitored for consistency and validity (e.g., check for errors, range checks, missing values) by the junior investigator. Moreover, the data and statistical code will be shared with the study board members.

#### Adverse event reporting and harms

Adverse events (AEs) are defined as any undesirable experience occurring to a subject during the study, whether or not considered related to the trial procedure or intervention. A serious adverse event (SAE) is any untoward medical occurrence or effect that results in death, is life threatening, requires (prolonged) hospitalization, and/or results in persistent or significant disability. All (S)AEs reported by the participant or observed by the researchers or therapists will be recorded. Events that meet the criteria of a SAE will be reported to the junior investigator and principal investigator within 24 h after coming to notice of the site investigator. The relatedness of a SAE to the trial procedure or intervention will be determined. Every month, the junior investigator checks with the site investigators if all (S)AEs have been reported. The final trial report will include a description of the SAEs, although no formal hypothesis testing will take place as low rates are expected [11].

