### Eligibility criteria

Patients are eligible if they (1) are between 18 and 70 years old; (2) have a primary diagnosis of PTSD as assessed by the Structural Clinical Interview for DSM-5-Clinician Version or Research Version (SCID-5-CV/RV); (3) have experienced the worst traumatic event (defined according to the DSM-5) before the age of 16 and agree that this trauma will be the focus of treatment; (4) have been experiencing PTSD symptoms for longer than 3 months; and (5) have an adequate proficiency in the language of the center or an adequate proficiency in the English language in case the center has English-speaking research assistants and therapists. Patients will be excluded if they (1) have experienced a trauma less than 6 months ago; (2) meet criteria for a current substance use disorder with a moderate or severe severity level (i.e., more than four symptoms), diagnosed with the SCID-5-CV/RV (after 6 weeks of abstinence, participation is possible); (3) fulfill the criteria of a psychotic disorder, diagnosed with the SCID-5-CV/RV; (4) have been diagnosed with the SCID-5-CV/RV with bipolar I disorder; (5) have acute suicide risk; (6) have an IQ below 80; (7) experience serious neurological problems (e.g., dementia); (8) are scheduled to start another form of PTSD treatment; (9) have received PTSD focused treatment within the past 3 months; (10) use benzodiazepine (after 3 weeks of abstinence, participation is possible); or (11) are not able to attend the treatment sessions of both randomization possibilities (i.e., 12 sessions of 90 min within 8 weeks and 12 sessions of 90 min within 16 weeks). In addition, patients will not start treatment unless their medication use has been stable for at least 3 weeks. Finally, patients are not allowed to start any form of psychological treatment or medication between the screening period and 24 weeks after the start of the study treatment (non-PTSD focused supportive treatment may be continued during the screening and waitlist period).

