#### Ancillary and post-trial care

In case of acute crisis during the study, patients may alter their medication or engage in another form of psychological treatment in addition to the study treatment. This will not lead to exclusion from the study. Details of medication use and other psychological treatments next to the study treatment will be recorded.

Following the assessment at 24 weeks after start of the treatment, the therapist will see the patient for an evaluation to determine if more treatment is needed. The type, intensity, and frequency of a potential further treatment will be determined based on the needs of the patient and the possibilities of the center. Details of any further treatment will be recorded. Note that further treatment might focus on other problems than PTSD.

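### A suicide attempt or self-harm that is not life threatening, needs no admission and leaves no lasting disability is only an ordinary AE, with no 24-hour report, stated relatedness assessment or promised place in the final report

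*Protocol article*

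**What the plan says.** The protocol article, under Adverse event reporting and harms, uses two tiers.

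- **AE.** The definition is broad and does not depend on relatedness: "Adverse events (AEs) are defined as any undesirable experience occurring to a subject during the study". The recording rule covers both tiers: "All (S)AEs reported by the participant or observed by the researchers or therapists will be recorded". So does the completeness check: "Every month, the junior investigator checks with the site investigators if all (S)AEs have been reported".
- **SAE.** An untoward medical occurrence or effect is serious if it "results in death, is life threatening, requires (prolonged) hospitalization, and/or results in persistent or significant disability". Three further steps are written for this tier only. The first is speed: "Events that meet the criteria of a SAE will be reported to the junior investigator and principal investigator within 24 h". The second is that relatedness to the trial procedure or intervention is determined. The third is that the final report describes the SAEs, without hypothesis tests because few are expected.

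Three other places set the context. Eligibility criteria exclude patients who "have acute suicide risk". Ancillary and post-trial care states: "In case of acute crisis during the study, patients may alter their medication or engage in another form of psychological treatment", and keeps such patients in the study. Data monitoring and management states that "there is no data monitory committee as the study involves minimal risk" and that there will be no independent audit.

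**The concern.** The SAE list is complete as printed. It has no clause for other medically important events, and it does not name suicide attempt or self-harm. The SAE label alone triggers fast reporting, the relatedness determination and the promised description. An event of evident safety interest in this population can therefore fall outside all three because of how it was managed and how severe it was judged to be.

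The stake is oversight during the trial and completeness of the safety description afterwards. With no monitoring committee, no independent audit and no interim analysis (Statistical analyses), the SAE route is the only 24-hour signal that the article describes. The Discussion says that therapists would be encouraged to consider twice-weekly sessions if outcomes improve. A reader weighing that advice would want to see suicide attempts and self-harm by frequency arm, and the article does not promise this.

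**Working it through.** No arithmetic applies: the plan gives no rate for these events and the point depends on none. The check is to run the event through the printed definitions.

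**Step 1. Classify a suicide attempt or act of self-harm.** The four criteria are alternatives, so meeting any one is enough.

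| Course of the event | Criterion met | Class |
|---|---|---|
| Fatal | Death | SAE |
| Life threatening, not admitted | Life threatening | SAE |
| Not life threatening, admitted | Hospitalization | SAE |
| Neither, but lasting or significant disability | Disability | SAE |
| None of these | None | AE only |

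Only the last row is a gap.

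**Step 2. Compare what each class receives.**

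| Step in the article | SAE | AE only |
|---|---|---|
| Recorded | Yes | Yes |
| Monthly check that it has been reported | Yes | Yes |
| Report to junior and principal investigator within 24 hours | Yes | No |
| Relatedness determined | Yes | Not stated |
| Described in the final report | Yes | Not promised |

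An event in the last row of Step 1 gets the first two steps and is promised none of the other three.

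**Step 3. Look for another provision that fills the gap.** The only mention of suicide in the article is the entry criterion, which governs who enters and not what happens later. The acute-crisis paragraph requires changes in medication and other psychological treatment to be recorded, but it says nothing about classifying the underlying event. The study board meets monthly and reviews progress, but no task of reviewing individual AEs is given to it. Therapists have weekly supervision, which is clinical support and not a reporting route. None of these supplies the three missing steps.

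**The case against.** The strongest objection is that this is a condensed article. Event-specific classification rules are the kind of detail left to the full protocol, and version 2.1 is not shown. It may well contain such a rule. But the article prints an operative, closed definition and ties specific duties to it. The point is about the consequence of that stated rule, and the sponsor can answer it by citing the full text.

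The second objection is that existing handling is better than the concern suggests: AEs are defined broadly, all are recorded, and completeness is checked monthly. This stands. No data need be lost. What is missing is speed, a relatedness determination and a commitment to report.

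A reader might infer more than the documents support:

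- *That any attempt managed without admission escapes the 24-hour rule.* It does not. A life-threatening attempt, or one with lasting disability, is an SAE without admission.
- *That self-harm is an expected harm of these treatments or of denser sessions.* The article does not say so. It describes both interventions as safe for these patients and expects few SAEs. Its acute-crisis paragraph mentions neither suicide nor self-harm.
- *That local admission practice in three countries biases the comparison of arms.* Randomization is blocked within each center, so local practice applies to all arms at a site. It affects how complete and uniform the SAE count is; it does not by itself create an imbalance.
- *That the plan's safety comparison of frequencies is undermined.* The listed objectives contain no such comparison, and SAE reporting is descriptive.

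A further fair objection is that making every act of self-harm an expedited SAE could swamp the route in a trial that does not exclude personality disorders. That is accepted, and the fix below avoids it.

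**Conclusion.** The gap is real but narrow. As printed, a suicide attempt or self-harm that is not life threatening, does not lead to hospitalization and leaves no lasting disability is recorded and covered by the monthly check. It has no 24-hour report, no stated relatedness determination and no promised place in the final report. Given the suicide-risk exclusion, the provision for acute crises and the absence of a monitoring committee, closing the gap is worthwhile.

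Its size in patients cannot be given: the documents contain no rate of suicide attempts or self-harm, and any count would be a guess. The primary analysis, the power and the treatment comparison are unaffected.

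The conclusion assumes that the article's definition is the one in force and that version 2.1 adds no rule for these events. It is best treated as a cheap improvement, not a correction of an error.

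**What to change.** Make two changes under Adverse event reporting and harms:

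1. Add suicide attempts, whether or not the patient is admitted, to the events that get the 24-hour report and the relatedness determination. Acts of self-harm that are not suicide attempts and meet none of the four criteria stay in the AE tier.
2. Commit the final report to a description of all recorded suicide attempts and self-harm events by frequency arm (once weekly, twice weekly), without formal testing.

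If version 2.1 already provides for this, cite the provision instead.

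**Cost.** One formal amendment, which the Design section says goes to the ethics committees of each country, and a few more expedited reports. No new data collection is needed, because AEs are already recorded and earlier records can be reviewed for these events. That review assumes the records describe each event well enough to identify it. Recruitment was still open according to Trial status, so the faster route could apply to later patients. No treatment or clinical rule changes.
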